### Sample Size Determination

Sample size was calculated based on the results of quasi-experimental study for INDAK where we compared the mean difference in ADAS-Cog, the primary outcome, from baseline and after 1-year follow-up between intervention and control groups. In that study, ADAS-Cog decreased by 3.16 (SD = 5.97) in the intervention group and 0.91 (SD = 8.69) in the control group (15), with an α error of 5% and β of 5% (power of 95%), and a one-tailed alternating hypothesis in favor of the intervention group, the sample size calculated is 136 per group or 272 for two groups (intervention and control). To account for clustering, a design effect of two will be adopted. This means that the total sample will be 544, with 272 participants per group. Allowing for 10% dropout, the final total sample size required in this study is 605 participants. This will be divided into 20–25 clusters per treatment arm. One cluster will have 12–15 participants, a range we found to be optimum for the intervention in the previous observational study. For MRI, at least 20% of the sample will undergo MRI, selected randomly from both intervention and control arm. This will be proportionally allocated to both arms. The estimated pilot size is 60 participants or 30 per group, expecting higher dropouts; 20% allowance was added giving a final pilot size of at least 72 or 36 per group. The pilot phase is to assess the acceptability of combined interventions (i.e., INDAK, vascular risk management, and nutrition counseling), determine adherence and dropout rates, as well as identify challenges and feasibility of conducting and advancing our research findings with neuroimaging outcomes.

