#### Data Management and Statistical Analysis

Data will be encoded independently by two research associates, and inconsistencies will be double checked with the data source to ensure data accuracy. All tests (primary and secondary outcomes) will be analyzed as independent continuous measures; additionally, we will also analyze for executive function composite (EFC) score derived by dividing independent test scores with their maximum possible scores and summing across tests for EFC, as was done in previous studies (63–65).

The study will employ univariate, bivariate, and multivariate statistics. For univariate, descriptive statistics (mean/SD; frequencies/percentages) will be used to summarize sociodemographic and other baseline characteristics. The bivariate analyses that examine underlying relationships between the outcomes and other clinical characteristics are the following: independent *t*-test for continuous variables and Chi square test (or Fisher exact test when ≤ 20 of the cells have the expected count <5) for categorical variables to compare baseline data between the intervention and control groups. Pairwise comparison of the randomization groups per timepoint will also be done to explore differences at different times using independent *t*-test. For multivariate analyses, the study would estimate the effect from baseline to follow-up at 12 months between randomization groups. Since the participants will be assessed three times (at baseline, 6th and 12th months), the study will be using multilevel mixed models to test the significance between group means but controlling for possible confounders (i.e., when age, sex, and education were not successfully controlled for in the randomization design). Necessary diagnostics will also be considered. This multilevel model is appropriate as it can take into account the clustering effect, and the number of clusters in this study is moderately sized (25–30 clusters per arm).

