To analyze for the secondary outcomes, RM-ANOVA/RM-ANCOVA will also be used. Point estimates and their corresponding confidence intervals will be evaluated to assess precision and power. Very wide confidence intervals will signify underpowered analyses. Sensitivity analysis will be conducted including imputation of missing data using last observation carried forward or mean imputation. Data management will primarily be the responsibility of the research team. All data will be securely stored and accessible only to the researchers in compliance with the ethics approval of the study.

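### The sizing uses a one-tailed 5% test that is not carried into the primary analysis; 605 participants give about 80% power on that test, about 70% if it is two-sided, and not the stated 95%

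*Protocol article*

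**What the plan says.** The section Sample Size Determination takes its inputs from an earlier quasi-experimental study of the dance programme: "ADAS-Cog decreased by 3.16 (SD = 5.97) in the intervention group" and "0.91 (SD = 8.69) in the control group". It sets alpha at 5% and power at 95%, adopts "a one-tailed alternating hypothesis in favor of the intervention group", and concludes that "the sample size calculated is 136 per group or 272 for two groups". It then states that "a design effect of two will be adopted", giving 544, and allows for 10% dropout, giving 605.

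The section Data Management and Statistical Analysis says of the main comparison that "the study will be using multilevel mixed models to test the significance between group means". It adds independent t-tests for baseline comparisons and for exploring group differences at each time point, and repeated-measures ANOVA or ANCOVA for the secondary outcomes. On intervals it says: "Point estimates and their corresponding confidence intervals will be evaluated to assess precision and power". It states no sidedness, alpha or confidence level for any of these.

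The Introduction states a directional hypothesis, that cognition will be better with the intervention than in controls. This agrees with the direction used in the sizing.

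**The concern.** The only decision criterion in the document is the one-tailed 5% test in the sizing sentence. It is a demanding choice to defend: for a claim of benefit it carries the same false-positive risk as a two-sided 10% test. Nothing in the description of the primary analysis repeats it. A colleague reading an unqualified mixed-model comparison would normally take it as two-sided at 5%, so the sizing and the analysis may rest on different tests.

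What is at stake is the power figure on which the trial is justified. If the figure belongs to a different test from the one used, or does not follow from its own inputs, then the chance of missing the assumed effect is understated. Correcting the 95% without settling the sidedness would leave the same ambiguity around the new figure.

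**Working it through.** **Inputs, all from Sample Size Determination.** Mean change 3.16 (SD 5.97) against 0.91 (SD 8.69); alpha 5%, one-tailed; stated power 95%; 136 per group; design effect 2; dropout 10%.

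- Difference: 3.16 − 0.91 = 2.25.
- Sum of variances: 5.97² + 8.69² = 35.641 + 75.516 = 111.157.

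**Reproducing the plan's figure.** n per group = (z_alpha + z_power)² × 111.157 / 2.25².

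- One-tailed 5%, 95% power (as stated): (1.645 + 1.645)² × 111.157 / 5.0625 = 237.6, so 238. This is not 136. With the design effect and two arms, 238 × 2 × 2 = 952; 952 / 0.9 = 1,058.
- One-tailed 5%, 80% power: (1.645 + 0.842)² × 111.157 / 5.0625 = 135.8, so 136. Then 136 × 2 × 2 = 544 and 544 / 0.9 = 604.4, so 605. All of the plan's figures follow.

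The printed sample size is therefore the one for 80% power.

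**Power at the planned enrolment.** 605 enrolled less 10% gives 544 evaluable, 272 per arm; divided by the design effect of 2, 136 effective per arm.

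- SE = √(111.157 / 136) = 0.904.
- Difference / SE = 2.25 / 0.904 = 2.489.

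| Test at 5% | Calculation | Power |
|---|---|---|
| One-tailed | Φ(2.489 − 1.645) | 80.1% |
| Two-sided | Φ(2.489 − 1.960) | 70.2% |
| One-tailed, t with 38 or 48 df | noncentral t | 78.8% or 79.1% |
| Two-sided, t with 38 or 48 df | noncentral t | 67.9% or 68.4% |

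The degrees of freedom are the number of clusters minus 2, with 20 to 25 clusters per arm as in the sizing section.

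If nobody dropped out (605 evaluable, 151.25 effective per arm), power would be 83.6% one-tailed and 74.7% two-sided, still short of 95%.

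**Splitting the shortfall.**

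- From 95% to 80%: the sample size does not match the stated beta. This arises on the plan's own one-tailed test.
- From 80% to 70%: the step from a one-tailed to a two-sided 5% test.
- A trial really sized at 238 per group would still have about 91% power two-sided: √(238 × 5.0625 / 111.157) = 3.292, and Φ(3.292 − 1.960) = 0.91.

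**Two-sided sizes, for reference.** 80% power needs 173 per group, or 173 × 4 / 0.9 = 769 in total. 95% power needs 286 per group, or 286 × 4 / 0.9 = 1,272 in total.

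**The case against.** The strongest reply is that the article is silent on the sidedness of the analysis, and silence is not contradiction. Alpha, sidedness and interval level for the primary contrast are commonly left to a statistical analysis plan, which is not shown. Hypothesis and sizing agree on direction, and a mixed-model contrast can be tested one-tailed. Choosing a one-tailed test is a declared design decision. All of this stands, and it limits the point in four ways.

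- A reader might infer that the analysis section specifies two-sided tests and so contradicts the sizing. It does not. Two-sided 5% is a conventional reading, and the 70% is conditional on it.
- A reader might cite the repeated-measures ANOVA, whose F-test has no direction, or the t-tests, as evidence of a two-sided primary test. The first is assigned to secondary outcomes; the second are for baseline and exploratory comparisons. Neither bears on the primary contrast.
- A reader might infer that the one-tailed sizing is why 605 participants give about 70% power when 95% is stated. Sidedness accounts only for the last step, from 80% to 70%.
- A reader might expect the test and the reported interval to disagree. If a 95% interval were set beside a one-tailed 5% test, they would disagree for z between 1.645 and 1.960, about 10% of trials under the assumed effect (80.1% − 70.2%). But the article gives no interval level and uses intervals to judge precision and power, not as a rule for declaring benefit. Nor would one-tailed testing hide a harmful direction, since estimates and intervals are planned.

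What the reply does not meet is the stated power. The 95% is wrong under the article's own one-tailed test, and no later choice of sidedness can make it right.

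**Conclusion.** The point holds in a limited form. The one-tailed 5% criterion is stated once, in the sizing, and is not attached to the primary mixed-model test. At 605 participants that criterion gives about 80% power, against 95% stated. If the primary test is two-sided at 5%, power is about 70%, or about 68% with cluster-level degrees of freedom.

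These figures rest on the plan's assumed difference and SDs, a design effect of exactly 2, 10% dropout, and a comparison of mean changes as used in the sizing. A mixed model that gains precision from baseline or repeated measures could do somewhat better; the documents give no correlation from which to calculate this. The correction should be made, but it is one of stated power and of an undeclared test, not evidence that two stated tests conflict.

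**What to change.** In Data Management and Statistical Analysis, state that the month-12 ADAS-Cog contrast from the mixed model is tested two-sided at 5% and reported with a 95% confidence interval. In Sample Size Determination, replace the 95% by the power of that test at 605 participants, about 70% on the plan's inputs. The enrolment target can stay as it is.

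If the sponsor keeps the one-tailed 5% test, the analysis section should say so and report the matching 90% interval, so that test and interval agree. The sizing section should then state about 80% power.

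Either way the change is wording in two paragraphs, with no added participants. The cost is a less favourable stated power. Study Status and Trial Registration reports that recruitment stopped after eight clusters and was expected to resume, so at the time of the article the choice could still be fixed before the main study's outcomes were known.

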### Recruitment and Assessment Visits

Based on power calculations specified above, we aim to enroll a total of 605 community-dwelling participants based on specified inclusion and exclusion criteria, in which, at least 72 participants are part of a pilot trial. At least 12–15 participants will be enrolled from each *barangay* (local community) to form one cluster. Pre-feasibility assessment will be conducted to assess if communities have resources to support recruitment and intervention such as availability of community health workers to assist in the study and venue for INDAK intervention. Recruitment will be done through public advertisements, and mobilizing community health workers will be mobilized to invite participants for screening. Schedule of visits, assessments, and interventions are outlined in Table 1.

**Table 1 T1:** Schedule of enrollment, intervention, and data collection.

**Study schedules**	**Pre-intervention**		**Intervention period**			
	**SV1**	**SV2**	**Month 0 (V1)**	**Month 3**	**Month 6 (V2)**	**Month 12 (V3)**
**Enrollment**
Screening assessment	x					
Informed consent	x					
Eligibility screening		x				
Allocation		x				
**Interventions**
INDAK			x	x	x	x
Nutrition counseling			x	x	x	
Vascular risks management			x	x	x	
**Data to be collected**
Sociodemographic data	x					
AD8	x					
MoCA-P	x					
Medical history		x			x	x
Physical and neurologic examination		x				
CDR		x			x	x
ADAS-Cog		x			x	x
Lawton's IADL		x				
NPI-Q		x				
MST			x		x	x
EFC			x		x	x
GDS			x		x	x
EQ-VAS			x		x	x
BBS			x		x	x
Anthropometric data			x		x	x
FBS			x		x	x
Lipid profile			x		x	x
ECG			x		x	x
APOE genotype			x			
MRI			x			x

*SV1 and SV2, screening visits 1–2; V1, month 0 is baseline; V2, assessment visit 2 done after the 6th month; V3, assessment visit 3 done after the 12th month; AD8, Ascertaining Dementia 8-Item Scale (AD8); MoCA-P, Montreal Cognitive Assessment Philippines; CDR, Clinical Dementia Rating Scale; ADAS-Cog, Alzheimer's Disease Assessment Scale—Cognitive; IADL, Lawton's Instrumental Activities of Daily Living; NPI-Q, Neuropsychiatric Inventory—Questionnaire; MST, Mnemonic Similarity Task; EFC, executive function composite; GDS, Geriatric Depression Scale; EQ-VAS, EuroQoL—Visual Analog Scale; BBS, Berg Balance Scale; FBS, fasting blood glucose; ECG, electrocardiogram; APOE, apolipoprotein-ε genotype; MRI, magnetic resonance imaging.*

*Sociodemographic data include gender, age, education, and income; anthropometric data include blood pressure, heart rate, body mass index (BMI), and abdominal circumference*.

#### Screening Visit 1 (SV1)

Delegated psychologists or nurses will obtain written consent from participants and their caregivers/family members prior to any procedures. Trained community health workers will administer the Filipino version of Ascertaining Dementia 8-item scale (AD8-P) (40), and psychologists will administer the Filipino version of the Montreal Cognitive Assessment (MoCA-P) (41). Participants with AD8-P ≥ 2 and/or MoCA-P ≥ 21 will proceed for the second screening visit. The cutoff scores for AD8-P will be used to determine reports of cognitive impairment ([name], manuscript submitted), while the cutoff scores for MoCA-P will be used to ensure that participants are not suspected to have dementia (41). Further screening will be done on SV2 to determine if cognitive impairment is sufficient to be diagnosed as MCI.

#### Screening Visit2 (SV2)

This is conducted within a week from SV1 to determine participant eligibility based on inclusion and exclusion criteria. The assessment team is comprised of a neurologist who will do a complete medical history, physical and neurologic examination, and the CDR (37), a nurse who will administer the NPI-Q and IADL to the collateral informant, and a psychologist who will administer ADAS—Cog to the participant to confirm a performance score of ≥1.5 SD below average.

#### Baseline Assessment (V1)

Once deemed eligible by the neurologist, the psychologist performs full neuropsychological test battery, described in detail at a section for outcome measures. For baseline data, nurses will collect information on sociodemographics (age, education, and income), vascular risk factors (hypertension, diabetes, dyslipidemia, cardiovascular diseases, cerebrovascular diseases, smoking, alcohol consumption, and physical inactivity), medical history and examination, medications, and anthropometric data (height, weight, abdominal circumference, blood pressure, pulse rates, etc.). The Berg Balance Scale will be conducted by a physical therapist to assess balance. Baseline laboratory tests include fasting blood sugar (FBS), lipid profile, electrocardiogram (ECG), apolipoprotein-ε (APOE) genotype, and MRI for all participants will be conducted within 7–14 days after V1.

#### Mid-Intervention Assessment Visit (V2, 6th Month)

The psychologist will administer the primary and secondary outcome measures, except the BBS, which will be done by the physical therapist. Laboratory tests will be done on all participants to monitor and guide vascular risk management.

#### Post-Intervention Assessment Visit (V3, 12th Month)

The psychologist will administer the primary and secondary outcome measures, while the physical therapist will conduct the BBS. Laboratory tests will be repeated on all participants to monitor response to vascular risk management. Repeat MRI will only be done at V3. To ensure blinding, participants are asked not to discuss any intervention with the assessor.

### Outcome Measures

#### Primary Outcome Measures

Alzheimer's Disease Assessment Scale—Cognitive (ADAS-Cog) (42): This test consists of 11 tasks measuring the core cognitive deficits of Alzheimer's disease (AD), such as disturbances of memory, language, praxis, attention, visuospatial function, and other cognitive abilities. The ADAS-Cog was validated for use in the Filipino elderly with age- and education-stratified norms (35, 42). Its psychometric properties have good reliability (e.g., Cronbach's α 0.84; test–retest intraclass correlations/ICC: 0.93) and validity (MMSE-P: −0.88 and CDR: 0.81) (42, 43). Score ranges from 0 to 70 points, with lower scores indicating better cognitive function.Mnemonic Similarity Task (MST) (27): This task places strong demands on pattern separation, memory representation, and cognitive domains highly correlated with hippocampal function. It consists of two phases: encoding and test part. The encoding phase presents 128 colored photographs of objects on a computer screen to be classified by participants as either indoor or outdoor objects. The test phase consists of 192 items (64 targets, lures, and foil items each), in which participants engaged in a modified recognition task identifying each item as old, similar, or new items based on the encoding phase. Percentage accuracy is calculated, with higher percentage indicating better function. MST has been used in identifying hippocampal dysfunction associated with aging and dementia and found to be a sensitive and reliable tool in tracking the progression of cognitive decline and treatment efficacy (26, 27).Executive function composite (EFC) scales: This combines measures for verbal fluency task, which evaluates language and executive ability for categorical tasks (44); number cancellation task, which assesses visual modality and selective attention (45); and digit symbol substitution task (46) and trail making task (part B) (47), both of which examines visual scanning, executive function, processing, and psychomotor speed. Higher composite scores indicate better executive function. Each neuropsychological test demonstrate good validity and reliability to assess for executive function and track cognitive decline in older adults, for further details see references (48, 49).

#### Secondary Outcome Measures

Geriatric Depression Scale (GDS) (50): This is a brief 15-item scale, which evaluates depressive symptoms. The GDS score ranges from 0 to 15, with lower scores indicating fewer depressive symptoms. A validation study on the Filipino version of GDS found an adequate internal consistency with Cronbach's α of 0.84 and test re-test reliability ICC of 0.91 (50).EuroQoL—Visual Analog Scale (EQVAS) (51): This is used as self-rated scale to assess health-related quality of life. It is a brief, simple, and health-specific measure for quality of life (51, 52); therefore, it is practical for repeated use and appropriate for studies aiming to improve the health of participants. The scores range from 0 to 100, with higher rates indicating better perception of quality of health and life. It reported excellent test–retest reliability ICC of 0.87 and good validity in correlation with multi-item disease-specific QoL measures such as Medical Outcome Scale SF-20 (*r* = 0.70–0.72) and Rotterdam Symptom Check-List (*r* = 0.70) (53).Berg Balance Scale (BBS) (54): This consists of 14 tasks evaluating static and functional balance. The score ranges from 0 to 56, with higher scores indicating better function. BBS validation study conducted in older adults with mild to moderate dementia demonstrated excellent validity with Cronbach's α of 0.95 and ICC of 0.99 (55).Magnetic resonance imaging (MRI): This will be used to evaluate brain volume and functional connectivity.

### Randomization and Allocation Concealment

Cluster randomization will be used to ensure blinding and avoid contamination of group allocation (33), which was one of the challenges in the quasi-experimental study for INDAK (15). The rationale behind this design is to ensure sociocultural fitness of study to the close-knit and socially collective nature of the Filipino community. Communities are “*barangays*,” the smallest government unit in the Philippines, which is mostly characterized by a high population density (1). People live close to each other, acquainted and frequently interact with one another. They share the same public space and health services (e.g., health center, social center), therefore individual randomization within the same community will limit opportunity of concealing treatment allocation. A barangay is referred to as one cluster in this study.

Randomization will be done after baseline assessment is completed (V1); hence, allocation is concealed to the assessors. Clusters will be randomized to a 1:1 ratio by the study statistician using a computer-generated randomization method, constrained using minimization. That is, each community will be allocated with a probability of 0.8 to the group that minimizes the imbalance at baseline of the means of the primary outcomes. The study statistician will inform the primary investigator of group allocation, and the study coordinator will arrange the delivery of intervention. The outcome assessors will be blinded to group allocation. Their engagement with the participants will be limited only to the day of assessment.

### Multicomponent Intervention

The intervention team consists of physician, nutritionist, nurse, and dance teachers. The components of intervention are:

#### Improving Neurocognition Through Dance and Kinesthetics

Dance teachers are trained professional dance sport specialists with extensive experience in teaching ballroom dancing. INDAK consists of eight ballroom dances organized into 6-week modules with increasing complexity and intensity. The first week of each module introduces basic dance steps or figures then gradually progresses to more complex dance figures. The modules begin first with non-partnered dances allowing familiarization with one's own movement and followed later by dances with a partner, which is more complex and requiring interaction. The dance modules are Reggae, Cha-cha, Samba, Merengue, Bachata, Swing, Tango, and Salsa. The whole dance intervention lasts for 12 months. Each dance session is 60 min comprising of warm-up (5 min), dance proper (45 min), and cool down (10 min). Each session begins with review of previously learned dance figures, then integration of two to three new figures and then rehearsal of all learned dance figures with slow and fast music. The teacher shuffles the figures creating different sequences to test memory and cognitive ability. Concepts such as visualization, musicality exercise, improvisation, and dance recall are used. The nurse will use a logbook to register the frequency and duration of participation of each participant. From a previous study, adverse events were infrequent and limited to musculoskeletal pains in the first 2 weeks of the study (15). To ensure safety, a nurse will always be present at each session and liaise with local hospitals in case of unexpected adverse events. The nurse records vital signs (i.e., blood pressure and heart rate) of all participants before and after the dance. Compliance to INDAK intervention is defined as ≥80% attendance and completion of a full 60-min session for each attendance. Failure to participate or developing physical conditions that limits INDAK participation will be withdrawn from the study.

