## Methods and Analysis

### Study Design

FINOMAIN is a community-based, single-blind (outcome assessor), cluster-randomized controlled trial of a multicomponent intervention with two arms: an intervention and a control arm. The intervention arm will receive 12 months (1 h, twice per week) of dance training called INDAK, and intensive vascular risk management, which includes regular visits with the study physician for treatment and monitoring of vascular risks and nutrition counseling. A waitlisted control group will receive usual vascular care that includes general advice on management of risks and referral to the local health clinic. The protocol was prepared based on SPIRIT (Standard Protocol Items: Recommendations for Interventional Trials) guidelines (32), and the multicomponent intervention design followed the Medical Research Guidelines on the evaluation and development of complex interventions (33). A pilot trial will be carried out to assess the acceptability, safety, and feasibility of this multicomponent intervention. Ethics approval has been granted by St. Luke's—Institutional Ethics Review Committee (CT-18146) and was retrospectively registered at Clinicaltrials.gov with identifier NCT04301544 (trial registration data available at: https://clinicaltrials.gov/ct2/show/NCT04301544).

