#### Exclusion Criteria

Major sensory problems such as hearing and visual impairment that limits testing or dance participation.Any preexisting illness that in the judgment of the study physician precludes engagement in moderate physical activity.Intake of any anticholinergic drugs or cognitive-impairing/-enhancing medications.

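### Withdrawing non-dancers from the study is a post-randomisation exclusion that can occur in the intervention arm only, and it can bias the 12-month comparison

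*Protocol article*

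**What the plan says.** The rule stands in the Protocol article, Improving Neurocognition Through Dance and Kinesthetics: "Failure to participate or developing physical conditions that limits INDAK participation will be withdrawn from the study". The sentence before it defines adherence: "Compliance to INDAK intervention is defined as ≥80% attendance and completion of a full 60-min session for each attendance". The article does not say how the two sentences relate, or how much absence counts as failure to participate.

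Who can meet the trigger follows from Study Design. On one side, "The intervention arm will receive 12 months (1 h, twice per week) of dance training called INDAK". On the other, "A waitlisted control group will receive usual vascular care that includes general advice on management of risks and referral to the local health clinic". Controls have no dance sessions during follow-up.

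Randomization and Allocation Concealment places randomisation after the baseline assessment (Table 1 marks allocation at the second screening visit). On either timing it comes before anyone can fail to attend a class. At entry, both arms are screened for fitness; Exclusion Criteria lists "Any preexisting illness that in the judgment of the study physician precludes engagement in moderate physical activity".

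For the analysis, Data Management and Statistical Analysis says that "the study will be using multilevel mixed models to test the significance between group means", over baseline, month 6 and month 12. Last observation carried forward or mean imputation is named as sensitivity analysis. Sample Size Determination has one loss figure for the whole trial: "Allowing for 10% dropout, the final total sample size required in this study is 605 participants". The article does not state that outcomes are still collected after a withdrawal of this kind.

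**The concern.** As written, the rule removes people from the study, not merely from the dance classes. An intervention participant who develops a limiting condition in month 4 leaves the study. A control who develops the same condition in the same month stays and is assessed at months 6 and 12. The 12-month contrast then sets those who kept dancing and stayed fit against all controls, which is no longer the comparison that randomisation protects.

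The trigger may well be related to the primary outcome. The classes grow in complexity and deliberately test memory, so in people with mild cognitive impairment, stopping attendance could be an early sign of decline. New physical limitation could accompany decline too. If so, the retained intervention group looks better than the randomised group would have looked.

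This is not a gap that a separate analysis plan could fill. Such a plan can define an intention-to-treat set, but it cannot supply month-6 and month-12 scores that were never collected.

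**Working it through.** **Inputs from Sample Size Determination.** ADAS-Cog fell by 3.16 (SD 5.97) with the intervention and 0.91 (SD 8.69) in controls, so the planned difference is 3.16 − 0.91 = 2.25. One-sided α is 5%. The stated 136 per group times a design effect of 2 gives 272 per group and 544 in total; 544/0.9 = 604.4, rounded up to 605. These steps reproduce. (The 136 itself corresponds to 80% one-sided power, not the stated 95%. That is a separate matter and does not affect this point.)

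**Assumptions, not in the article.** A share p = 10–20% of the intervention arm is withdrawn with no month-12 data. The correlation between withdrawal risk and 12-month decline is r = 0.2–0.5. The true effect is nil. The 10% matches the main-trial dropout allowance and the 20% matches the pilot allowance; neither is an estimate of withdrawals under this rule.

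**Bias.** Removing the share p with the highest withdrawal risk shifts the mean of those retained by

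bias = r × SD × φ(z)/(1 − p), where z is the upper-p point of the standard normal.

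Only the intervention arm is selected, so SD = 5.97. The factor φ(z)/(1 − p) is 0.1755/0.90 = 0.195 at 10%, 0.2332/0.85 = 0.274 at 15% and 0.2800/0.80 = 0.350 at 20%.

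**Standard error.** The effective size is 272/2 = 136 per arm, with the intervention arm reduced to 136(1 − p):

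SE = √(5.97²/[136(1 − p)] + 8.69²/136) = 0.920, 0.929 and 0.940 for p = 10%, 15% and 20%.

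**Type I error** = 1 − Φ(1.645 − bias/SE). The gap between withdrawn and retained participants that each row implies is bias/p.

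| p | r | Bias (points) | Share of 2.25 | Implied gap (points) | One-sided error |
|---|---|---|---|---|---|
| 10% | 0.2 | 0.23 | 10% | 2.3 | 8.2% |
| 10% | 0.5 | 0.58 | 26% | 5.8 | 15.6% |
| 15% | 0.2 | 0.33 | 15% | 2.2 | 9.8% |
| 15% | 0.5 | 0.82 | 36% | 5.5 | 22% |
| 20% | 0.2 | 0.42 | 19% | 2.1 | 11.5% |
| 20% | 0.5 | 1.04 | 46% | 5.2 | 29.7% |

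At r = 0 the bias is nil and the error stays at 5%.

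**Cross-check in other terms.** Let bias = w × g, with w the share withdrawn and g how many points worse those withdrawn would have done. This version uses the pooled SD √((5.97² + 8.69²)/2) = 7.455 for the standard error. With w = 10% and g = 1, 2 or 4, the bias is 0.10, 0.20 or 0.40 and the error 6.2%, 7.6% or 11.2%. With w = 20%, the bias is 0.20, 0.40 or 0.80 and the error 7.5%, 11.0% or 20.9%. With g = −2, the bias is −0.20 (w = 10%) or −0.40 (w = 20%) and the error falls to 3.1% or 2.0%.

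**Whether the planned analysis repairs it.** The mixed model keeps baseline and any month-6 score, which helps if withdrawal depends only on what was observed. There is one visit between baseline and month 12, so anyone withdrawn before month 6 contributes baseline alone. Carrying the last score forward freezes a person who is declining at an earlier, better value. Mean imputation, if done within arm, assigns the average of those who stayed. Neither tests the assumption that matters.

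**The case against.** The strongest reply is that the direction is not shown. The article does not describe who would be withdrawn. People miss classes for reasons unrelated to cognition, illness precluding moderate activity is already excluded at entry in both arms, and the earlier INDAK study saw only infrequent musculoskeletal pain in the first two weeks. This stands: a reader might infer that the rule certainly inflates the effect, but the article supports only that it can, and probably would if those leaving were declining faster.

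The size is open as well. The top of the range needs withdrawn participants to do more than 5 points worse than those retained, over twice the planned effect. Using the pooled SD of 7.455 in the bias formula would give larger numbers, but selection acts on one arm whose own SD is 5.97. The figures also describe month-12 completers, and a model using earlier visits would give less bias. Nor can one say that the rule will use up the 10% dropout allowance: no withdrawal rate is given, and the pilot is meant to determine adherence and dropout.

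Finally, the sentence lacks a grammatical subject and sits in the description of the dance component, so a condensed article may be blurring stopping the dance with leaving follow-up. That is possible, but the words refer to the study, and the ambiguity is itself a reason to amend. None of these replies changes the structure: the trigger arises after randomisation and in one arm only.

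**Conclusion.** The rule is wrong as written. It is a post-randomisation exclusion confined to the intervention arm, and the planned mixed model and imputations do not reliably correct it. Under the stated assumptions, the spurious benefit is about 0.2–1.0 ADAS-Cog points (10–46% of the planned 2.25), and a nominal 5% one-sided test has a true error of about 8–30%. These are illustrations: the withdrawn share and the correlation are assumed, zero correlation gives no bias, a reversed association gives bias against the intervention, and observed visits would shrink the figures. The structural defect is certain; its direction is expected but not proven, and its size is unknown.

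**What to change.** Amend the sentence to separate stopping INDAK from leaving the study. It should say that stopping or not attending INDAK does not by itself end outcome assessment or remove anyone from the analysis; that such participants are still invited to the month-6 (V2) and month-12 (V3) assessments; and that they are analysed in the arm to which their barangay was randomised. Use the ≥80% attendance definition only for a secondary adherence analysis, and state that falling below it does not trigger withdrawal from follow-up.

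The clinical decision on who stops dancing, and any other ground for withdrawal, stays with the investigators. Restricting withdrawal to loss of consent alone would go further than the statistical need.

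The cost is a short amendment and some effort to trace non-attenders; both visits are already in Table 1. Study Status reports eight clusters (72 participants) randomised and the trial paused, so the change can be made before recruitment resumes.
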